## Methods and materials

### Study design

This is a case-control study using MDR to compare the movement patterns of 125 adults with a history of ACLR to that of 125 healthy controls. This study was reviewed and approved by the Pennsylvania State University Human Research Protection Program (HRPP) on May 18, 2022, and the IRB approval number is STUDY00020118. Eligibility criteria can be found in Table 1.

**Table 1 pone.0292675.t001:** Inclusion and exclusion criteria.

	ACL Group	Control Group
**Inclusion Criteria**	Age 18–40	Age 18–40
	History of ACL reconstruction between 9–24 months before recruitment	No history of lower extremity surgery
	Medically cleared to resume normal activities	
**Exclusion Criteria**	Age <18 or >40	Age <18 or >40
	Pregnant or institutionalized	Pregnant or institutionalized
	Current neuromuscular disease	Current neuromuscular disease
	Inability to provide informed consent	Inability to provide informed consent
	Inability to perform study activities	Inability to perform study activities
	Inability to walk or jump without a limp	Inability to walk or jump without a limp
	History of cerebral vascular accident	History of cerebral vascular accident
	History of knee or hip replacement	History of lower extremity surgery

Recruitment will occur through a retrospective review of Electronic Health Records (EHR) to identify patients that have undergone ACLR within the past 9–24 months. These participants will be mailed a recruitment letter explaining the study and providing contact information for our study coordinator. Once the potential participant makes initial contact and shows interest, a link will be sent to their email with a REDCap database eligibility screener [20]. Additional recruitment will occur through a prospective review of the surgical schedule for future ACL surgery candidates or patients that have recently undergone surgery, but have not yet been cleared for full activity. These participants will be provided with study flyers by a member of their medical team, and if interested will contact the study coordinator for potential future recruitment. Participation of all recruited patients is conditional upon successful clearance for full activity by their medical team at the time of participation.

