### Motion capture processing

MC data will be analyzed in two ways: 1) traditional MC data analysis will occur using variables extracted from averaged trial data, and 2) MC data will be subjected to the same machine learning algorithms outlined in the MDS processing section. The difference is that there are specific variables for MDS and MC. Extracted MC variables will include: internal rotation of the knee, pronation of the foot, the difference between inter-knee distance, forward displacement of the ACLR hip relative to the uninjured hip, sagittal and frontal hip and knee angular deficits at peak knee flexion angle, sagittal plane hip and knee displacement at peak knee extension angle, sagittal knee and hip displacements during weight acceptance, sagittal knee and hip displacement at midstance, and peak knee flexion and displacement. Data will be analyzed, and movement variables extracted from processed data using Visual 3D (C-Motion, Inc., Boyds, MD) and custom programs written in MatLab (The Mathworks, Inc., Natick, MA).

Traditional MC processing occurs by calculating inverse dynamics using Visual 3D and/or custom MatLab programs. Note that the selected tasks and variables represent measures that are expected to be identifiable using MDR, but not necessarily by MC. It is expected that MC will successfully measure the DJ2s, will be marginally successful at measuring STS, and will be unsuccessful at measuring gait speed on a level treadmill. The data will be processed using typical MC methods. MC data will be cleaned and preprocessed (including filling in missing data) using methods established for software programs Cortex 8 and Visual 3D. Data will be filtered using a 4th order, zero-lag low-pass Butterworth filter using MatLab filtfilt with a 10 Hz cutoff frequency.

The MC data will help us to effectively compare the accuracy of the MC system to that of MDR. Due to their heterogeneity, the two traditional sets of pre-processed data will not be statistically comparable. As such, we will use similar machine learning techniques to process the MC data, so that we are able to determine the accuracy and predictability of MC to correctly classify the ACLR group versus control. Accomplishing this will allow direct comparisons of discrimination, sensitivity and specificity for each of the techniques to successfully predict the control and ACLR groups.

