### Sample size justification and data analysis

This sample size calculation justifies our ability to assess the sensitivity and specificity of mD-SPA in its identification of the ACLR (i.e., case) and control groups. A total sample size of 250 (125 ACLR and 125 control) provides 88% power to detect a minimal change of 10% in sensitivity/specificity based on the exact binomial test. This sample size also has 80% power to detect an 8% improvement in prediction accuracy of mD-SPA relative to MC based on McNemar’s test. These calculations assume a minimal sensitivity and specificity of 90% for mD-SPA and that the proportion of discordant pairs of classification between the two measurement systems is 10%. The target significance level is assumed to be two-sided at 0.05 (PASS 2021 v*21*.*02*).

The continuous outcome times for DJ2, STS, and gait speed will be modeled using mixed effects models with person-specific random intercepts. These models will be weighted with the inverse of each person’s probability of belonging in their actual ACLR group, based on their separately modeled propensity for being in that group. The models will also adjust for the explanatory variables in the propensity score model, thereby enjoying the analytic property of being doubly robust. Statistical significance will be justified for multiplicity within the models of DJ2, STS, and gait speed using the standard Benjamini-Hochberg procedure to control for false discovery.

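### One motion-capture variable is defined by the operated side: it is undefined in controls and, if it feeds the MC classifier, it depends on the label being predicted

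*Protocol article*

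**What the plan says.** Motion capture processing sets out two analyses of the MC data. The first is a traditional analysis of variables taken from averaged trials. For the second, "MC data will be subjected to the same machine learning algorithms outlined in the MDS processing section". The text continues: "The difference is that there are specific variables for MDS and MC". The next sentence begins "Extracted MC variables will include: internal rotation of the knee, pronation of the foot" and goes on to include "forward displacement of the ACLR hip relative to the uninjured hip". The list is not restricted to the ACLR group.

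The stated purpose of the machine-learning analysis is to "determine the accuracy and predictability of MC to correctly classify the ACLR group versus control". Discrimination, sensitivity and specificity are then compared directly with those of MDR.

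Table 1 (Study design) gives as an inclusion criterion for controls "No history of lower extremity surgery". The article prints no rule for which limb of a control takes the place of the operated one.

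**The concern.** The definition has two consequences.

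- **In controls** there is no operated hip and no injured-versus-uninjured contrast, so the variable has no value until someone supplies a convention.
- **In cases** the sign of the difference is set by the operated side. Finding that side requires knowing that the person is a case, which is what the classifier is meant to predict.

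If the variable is a classifier input, MC is given information that would not exist when screening a person of unknown status. The section on micro-Doppler signature processing describes no such orientation for MDR, so the two systems would not be compared on equal terms. The likely direction is towards a better MC result, which makes a true MDR advantage harder to show. If the difficulty is noticed only at extraction and the variable is then dropped, the comparator is weakened by a late choice in a study that hypothesises MDR superiority.

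**Working it through.** **1. The plan's own figure for the MDR–MC comparison.** From Sample size justification and data analysis: an 8-point gain in accuracy, 10% discordant pairs, two-sided 0.05, McNemar's test, 80% power. With 90% sensitivity and specificity for MDR, implied MC accuracy is 0.90 − 0.08 = 0.82.

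Exact power = Σₘ Bin(m; n, 0.10) × P(test rejects in favour of MDR | m, q), where q = (0.10 + difference) / (2 × 0.10). For a difference of 0.08, q = 0.90. Power is 0.801 with n = 125 pairs and 0.990 with n = 250. The stated 80% is therefore reproduced with 125 pairs. The sentence itself refers to a total of 250; that is a separate matter, so both sizes are shown below.

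**2. How much could one variable carry?** The documents give no asymmetry, so these are assumptions: the side-to-side difference has SD 1 in both groups and mean 0 in controls; in cases it is shifted by d in the direction of the operated side; controls receive a random index limb.

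- Operated-side orientation: AUC = p = Φ(d/√2).
- Absolute asymmetry, |A| in cases against |C| in controls: |A| > |C| exactly when A − C and A + C have the same sign. These are independent, each with mean d and variance 2, so AUC = p² + (1 − p)².

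| d (assumed) | Operated-side orientation | Absolute asymmetry |
|---|---|---|
| 0 | 0.50 | 0.50 |
| 0.25 | 0.57 | 0.51 |
| 0.5 | 0.64 | 0.54 |
| 1.0 | 0.76 | 0.64 |
| 1.5 | 0.86 | 0.75 |

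For d = 0.5: p = Φ(0.354) = 0.638, and 0.638² + 0.362² = 0.407 + 0.131 = 0.538. The gap between the columns is what knowledge of the operated side adds. It is zero when d = 0.

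**3. What a gain in MC accuracy would do to the comparison.** MDR is held at 0.90 and discordance at 10%. Exact McNemar power to show MDR better:

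| MC accuracy | 125 pairs | 250 pairs |
|---|---|---|
| 0.82 | 0.80 | 0.99 |
| 0.84 | 0.48 | 0.83 |
| 0.86 | 0.20 | 0.44 |
| 0.90 | 0.01 | 0.01 |

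This table shows sensitivity only. The AUCs in step 2 cannot be converted into a gain in overall MC accuracy, because the variable is one of about ten listed and the classifier's other inputs and their correlations are not given.

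**The case against.** The strongest objection is that the text never says that this variable enters the classifier. The list speaks of extracted variables, which echoes the description of the traditional analysis. The section later says that the traditional data sets are not statistically comparable and gives this as the reason for machine learning. If the list serves only the traditional analysis, the leakage argument falls away and only the undefined value in controls remains. This stands as a limit on confidence. It does not remove the point, because the sentence on system-specific variables comes directly before the list, and the MDR section counts handcrafted features among the feature sets.

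A second objection is that a condensed article may leave the index limb for controls to the full protocol. That is fair for the missing rule. But the article does state a definition, and an index-limb rule would make it computable in controls without removing the dependence of the case orientation on the label.

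A reader might also infer more than the documents support:

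- **That the groups would be separated completely, or at 75% accuracy, with no true difference.** The first needs controls coded missing or constant, and a classifier able to use that code. The second needs signed values in cases and absolute values in controls (0.5 × 0.5 + 0.5 × 1.0 = 0.75). The article mentions neither coding. Its remark on filling in missing data concerns Cortex 8 and Visual 3D preprocessing.
- **That any convention for controls marks the group.** It does not. With no true operated-side asymmetry, a random index limb gives AUC 0.50, as does right minus left when centred on zero.
- **That bilateral reconstruction is a material problem.** Table 1 does not exclude it, but no frequency or effect is given.

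**Conclusion.** The point holds in a limited form. As worded, the variable cannot be computed in controls, and in cases it cannot be oriented without knowing group and operated side. If it is a classifier input, MC accuracy may be biased, most likely upwards and so against the MDR superiority hypothesis. A leak in that direction could hide a true MDR advantage; it would not create a false one.

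The size cannot be derived from the documents. It runs from none (random index limb, no true asymmetry), through modest (AUC 0.57 to 0.64 against 0.51 to 0.54 at assumed shifts of 0.25 to 0.5 SD), to complete separation only under a coding that the article does not mention. The documents do not support the stronger conclusion that the MDR–MC comparison is certainly invalid. Should-fix, moderate confidence.

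**What to change.** State whether the listed variables feed the MC classifier. For the classification analysis, define every side-to-side MC variable by one rule applied identically to all 250 participants and computed blind to group and operated side, for example left minus right or absolute asymmetry. Check the hip and knee angular deficits in the same list under that rule. Keep the operated-side version for description within the ACLR group only. Settle this before features are extracted.

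The cost is a sentence in the protocol and a change to the extraction code. The downside is that the classifier loses some directional information about the operated limb: at an assumed d of 0.5, absolute asymmetry gives AUC 0.54 where the operated-side version gives 0.64. If operated sides are evenly split, signed left minus right taken alone gives about 0.50, so its information is usable only by a classifier that can respond to magnitude. That loss is appropriate, since the side would be unknown when screening a person of unknown status.

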### Data collection

Upon arrival for their data collection session, the participant’s identification number will be checked, and they will fill out the Brief Pain Inventory Short Form, which will serve to identify any confounding pain effects on the testing protocol [21]. To mitigate the effects of possible fluctuations in pain perception, the pain survey will be administered immediately prior to the start of data collection.

Radar Micro-doppler signatures and biomechanical MC data will be simultaneously collected as participants perform a series of functional activities. Combining MC and MDR data collection presents unforeseen challenges. MC techniques are widely known and have developed a level of sophistication that allows for flexibility when positioning equipment in the data collection volume and selection of a marker set. Conversely, MDR is direction-specific in regard to the position of the antennae which in turn dictates the primary plane of action for the experimental task. Since body segment velocities for all three tasks in this experiment are primarily in the sagittal plane it is necessary to align the experimental apparatus with the MDR signal axis (0 deg from center of antennae). Once aligned, the challenge is to select a marker set where the experimental apparatus doesn’t obscure markers. The solution is to place extra tracking markers on the pelvis, forearms (wrists), and head. These markers can then be used as reference points in Visual 3D to create virtual markers, which are then used along with the actual markers to create the skeletal model.

The marker set used to produce the Visual 3D skeletal model (virtual and actual) consists of 34 markers which are used to calculate all joint and segment angles, and their time derivatives. Bilateral lower-body markers consist of medial and lateral toes (2nd metatarsal and little toe), heel (calcaneus), medial and lateral ankle (malleolus), and medial and lateral knee (Tibial condyles). Trunk markers consist of right and left (R&L) anterior superior iliac spine, R&L posterior superior iliac spine, R&L shoulder (acromion), lower neck (C7), mid-trunk (T8), and sternal notch. Bilateral arm markers consist of the medial and lateral elbow (humeral medial and lateral epicondyles) and the wrist (radial and ulnar styloid processes). Head markers consist of the left and right zygomatic arches directly anterior to the inter-aural axis and top of the head.

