Data from the ACLR and control groups will be collected by the MDR and MC systems simultaneously by a triggering system that matches the data collection on the time axis prior to the onset of movement. Participants will be asked to perform five trials of each of the following three tasks: Two-legged drop jumps (DJ2) from a low box (30cm), standing from a seated position, i.e., sit-to-stand (STS), and continuous gait on a treadmill. Participants will be asked to wear appropriate clothing and footwear for exercise training. Each task will be demonstrated by a research team member and participants will be given time to practice before data collection begins. Task order will be randomized, and all five trials of each task will be performed as a block. Participants will be given time to rest between practice and trial performances and in between trials during data collection to minimize fatigue effects. Any trial that deviates from the instructed methods will be evaluated and repeated before continuing. The three tasks will be completed in the frontal plane or 0 degrees with respect to the MDR.

The DJ2 task is usually performed without incident in clinically recovered patients during late or post-ACL reconstruction rehabilitation, while the STS and gait are typically applied earlier in the rehabilitation periods for patients who have not fully cleared rehabilitation. The three tasks selected are typical of ACLR rehabilitation, can be performed in any clinic, and cover a range of performance abilities.

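### One listed motion-capture variable can be computed only from the group label and operated side, is undefined for controls, and can bias motion-capture accuracy in the comparison with radar

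*Protocol article*

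**What the plan says.** Under Motion capture processing, the protocol article sets out two analyses of the MC recordings: a traditional one on variables from averaged trials, and a machine-learning one like that used for the radar signatures. It notes that MC and radar each have their own variables and then lists the MC variables. One of them is "forward displacement of the ACLR hip relative to the uninjured hip". Extraction uses Visual 3D and custom MatLab programs.

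On the steps before extraction it says "MC data will be cleaned and preprocessed (including filling in missing data", names the methods established for Cortex 8 and Visual 3D, and fixes one Butterworth filter for all data. It does not say who does this work, how much of it is manual, or whether group is known at the time.

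The section ends by stating the purpose: to find how accurately MC assigns people to the ACLR or control group, and to compare discrimination, sensitivity and specificity directly with MDR. The sample size section gives that comparison "80% power to detect an 8% improvement in prediction accuracy of mD-SPA relative to MC based on McNemar’s test".

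**The concern.** In an accuracy study, what is fed to the test must be obtainable without knowing the answer. The reference here is membership of the ACLR or control group. A variable defined by the ACLR hip and the uninjured hip takes that reference as an input. Controls have neither an ACLR hip nor, in this sense, an opposite uninjured one, so the variable must be left missing, given a default, or computed under an unstated side convention.

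Each choice matters. If the value is missing or constant in controls, the classifier can read group from that pattern alone. If cases are oriented by the operated side and controls by some other convention, the two groups are measured by different rules. In either case MC's sensitivity and specificity no longer describe what MC could do for a person of unknown status, which is the screening use the article has in mind. The MDR-versus-MC contrast then inherits the distortion, and the paired test cannot remove it.

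**Working it through.** **1. Does the variable need the label?** The relevant statements in Motion capture processing, side by side:

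| Statement | What it requires |
|---|---|
| Listed variable: "forward displacement of the ACLR hip relative to the uninjured hip" | Case status and operated side; no value for a control |
| MC data are used to classify ACLR versus control | Predictors defined in the same way for both groups |
| MC accuracy is compared directly with MDR | MC accuracy free of label information |

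The first statement conflicts with the second, and the third carries the conflict into the main comparison. The list also includes hip and knee angular deficits, with no statement of the limb or norm they are measured against. They may have the same problem and should be checked.

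**2. The plan's own power figures.** Inputs from Sample size justification and data analysis: 125 per group, two-sided 0.05, mD-SPA sensitivity and specificity of at least 90%, discordant proportion 10%.

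- *Exact binomial, 10-point change, stated 88%.* I read this as p0 = 0.80 against p1 = 0.90 with n = 125. The upper rejection region is X ≥ 109, and P(X ≥ 109 | 0.90) = 0.881. The stated figure reproduces.
- *McNemar, 8-point improvement, stated 80%.* From p10 + p01 = 0.10 and p10 − p01 = 0.08, p10 = 0.09 and p01 = 0.01. The number of discordant pairs is D ~ Bin(n, 0.10). Given D, the number favouring MDR is Bin(D, p10/0.10), tested exactly against 0.5. Summed over D, power is 0.801 for n = 125 and 0.990 for n = 250. The stated 80% therefore fits 125 pairs, that is, one group.

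**3. Illustration only.** The documents give no size for any shift in MC accuracy, so the shifts below are assumptions. The model is the same McNemar model, with 10% discordance.

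*If the shift lowers MC accuracy and there is no true difference,* the chance of a significant result in MDR's favour is:

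| Assumed loss for MC | 125 pairs | 250 pairs |
|---|---|---|
| 0 points | 1.2% | 1.5% |
| 1 point | 2.9% | 4.6% |
| 2 points | 6.1% | 11.9% |
| 3 points | 11.6% | 25.0% |

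*If the shift raises MC accuracy by 3 points and the true MDR advantage is 8 points,* the apparent advantage is 8 − 3 = 5 points. Power falls from 80.1% to 32.4% on 125 pairs, and from 99.0% to 65.3% on 250.

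The tables show only that a shift of a few points in either direction would matter. They are not estimates for this study.

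**The case against.** **The article is condensed.** Side conventions and masking may be in the full protocol. This stands for masking: the article neither describes masked processing nor plans unmasked processing, so its silence is not counted. It does not stand for the variable, which the article itself defines in a way that cannot apply to controls.

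**The variable may belong only to the traditional analysis.** This is possible. However, the list follows directly on the statement that the machine-learning analysis has its own MC variables, and nothing keeps this one out of the classifier. One sentence from the authors would settle it.

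**Side can enter a program as a coded field that nobody sees.** This is correct, and it answers any worry about a person's knowledge. It does not answer the definition: a hidden field that exists only for cases still carries the label into the predictor.

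**Stronger readings that the article does not support.**

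- A reader might infer that cleaning and gap filling are planned with case status in view. Variables are extracted after processing, nothing in cleaning needs the operated side, and the text names standard software methods and one fixed filter.
- A reader might infer that human handling falls mainly on MC because MDR uses an existing algorithm. The section on micro-Doppler signature processing also describes handcrafted radar features and a newly proposed reduction technique, so analysts make choices on both sides.
- The rule "Any trial that deviates from the instructed methods will be evaluated and repeated before continuing" might look like a route for bias against MC. The two systems record simultaneously, so a repeat affects both.
- The arrival procedure, in which the "identification number will be checked", says nothing about masking in either direction.

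**Conclusion.** The point holds in a limited form. One listed MC variable takes the reference label and operated side as inputs and is undefined for controls, although MC variables serve to classify ACLR versus control and MC accuracy is compared with MDR. Followed as written, this can bias MC sensitivity and specificity and hence the head-to-head result.

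The direction and size cannot be derived from the documents. Leaked group information would flatter MC, while an ill-defined or noisy value in controls could hurt it. The conclusion assumes that the listed variable is among the classifier's inputs, which is the natural reading but is not stated outright. The change should be made before processing starts. Confidence is medium because the full protocol may already contain a side rule.

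**What to change.** 1. **Redefine the variable.** Replace this and any other side-referenced MC variable with a rule that ignores group and is identical for cases and controls. Examples are the absolute between-limb difference, or an index limb assigned at random or by dominance in everyone. Giving controls a sham operated side while cases keep the true one is not enough, because the case value would still depend on the label.
2. **Code the files.** Run any manual cleaning, gap filling and variable extraction on files that carry participant ID and limb A/B only, without group.
3. **Lock features, then merge.** Lock the processed feature files of both systems before group labels are merged for training and testing. The lock has to be on features, not on final classifications, because training the classifier needs the labels.
4. **Keep the clinical variable for description.** The operated-versus-uninjured version can be reported within the ACLR group, outside the classifier.

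The cost is a coding script, a key file with someone to hold it, and a paragraph in the processing procedure. The classifier loses the operated-versus-uninjured direction, which would not be available for a person of unknown status in any case. No extra visits or participants are needed.
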